### Design

To investigate the effect of the intervention, a randomized controlled trial (trial registration: ISRCTN33869008) will be conducted at 20 surgical departments in southeast Sweden. The trial will follow a two-arm single-blind parallel-group design. Figures 1 and 2 offer an overview of the design in the form of a SPIRIT (Standard Protocol Items: Recommendations for Interventional Trials) figure and CONSORT (Consolidated Standards of Reporting Trials) flowchart, respectively. The trial began in October 2018.

#### Intervention and Control Settings

One group will be given access to the novel intervention, while the other group will not be given access to the intervention. Both groups will have access to the surgical departments’ current routine for smoking cessation prior to surgery. The current routine varies slightly among departments, but generally consists of referring individuals to either the national quit-smoking helpline or their local primary health care provider. None of the participating departments’ supply any additional cessation help.

#### Recruitment

The study will be advertised through printed material provided to patients when they meet with a nurse or operation planner prior to surgery. During this meeting, the nurse or operation planner will emphasize on the importance of smoking cessation prior to surgery and hand out the printed material about the trial. Patients will also be informed about other support they can receive for smoking cessation.

Patients who want more information about the study will have to send an SMS message with a specific code to a dedicated phone number. In response, they will receive a message containing a hyperlink to a webpage that contains more information about the study. On the webpage, participants who wish to partake in the study will complete the informed consent form, following which a baseline questionnaire will be presented to them. Participants will be randomized once the baseline questionnaire has been completed.

**Figure 1 figure1:**
[figure not shown]
SPIRIT (Standard Protocol Items: Recommendations for Interventional Trials) checklist.

**Figure 2 figure2:**
[figure not shown]
CONSORT (Consolidated Standards of Reporting Trials) flowchart.

Recruitment will be continuous for a minimum of 12 months and a maximum of 30 months. After the initial 12 months, the recruitment period will be extended in 6-month periods until a sufficient number of participants have been recruited according to power calculations (to a maximum of the 30 months).

This protocol was approved by the ethical review board in Linköping (DNR 2018/316-31).

#### Eligibility

Smokers undergoing elective surgery who own a mobile phone will be included in the study. No age restrictions will be applied. Patients will be excluded if they inform the operation planners that they do not smoke or if they report that they smoke zero cigarettes when filling out the baseline questionnaire.

#### Randomization

Randomization will be fully computerized, not employ any strata or blocks, and not be possible to subvert because all subsequent study processes are fully automated. The trial is single blind, as participants will be aware of group allocation. Since the randomization procedure is automated, group allocation will not be disclosed to individuals responsible for the research project (researchers and surgical staff).

#### Follow-Up

Six weeks after randomization, mediating factors will be assessed through a questionnaire. At 3, 6, and 12 months after randomization, smoking-cessation outcomes and mediating factors will be assessed through questionnaires. In all cases, hyperlinks to the questionnaires will be sent to participants’ mobile phones via an SMS. Two reminders will be sent, after which phone calls will be made to collect the primary outcome measures only. A maximum of five phone calls will be made to each participant at each follow-up stage.

#### Measures

All questions asked at baseline and subsequent follow-ups can be found in Multimedia Appendix 1.

Hypothesis 1:

Primary outcome measures: Prolonged abstinence and point prevalence of smoking abstinence.Secondary outcome measures: Seven-day point prevalence of smoking abstinence, mean number of quit attempts since participation in the trial, number of uses of other smoking-cessation services since joining the trial, and number of cigarettes smoked weekly (if still smoking).

Hypothesis 2:

Mediation measures: Importance and self-efficacy of quitting and staying smoke free.

Prolonged abstinence is defined according to the Russell standard definition [38], applying the usual threshold of not smoking more than 5 cigarettes in the past 8 weeks (thus allowing for a 4-week grace period). The 8-week period is then adjusted to 5 and 11 months at 6- and 12-months of follow-up, respectively. Point prevalence of smoking abstinence is defined as not smoking any cigarette in the past 4 weeks, which aims to capture delayed effects of the intervention, as suggested by the Society for Research on Nicotine and Tobacco [39]. Importance and self-efficacy will be investigated by two questions (Multimedia Appendix 1) rated on a scale of 1 to 10.

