### Previous Research and Findings

Over the past few years, it has become more evident that short message service (SMS)–based interventions can help individuals quit smoking. In a Cochrane review from 2016 [14], it was indicated that long-term quit rates increased by 67% among those who were given access to SMS-based smoking-cessation interventions compared to those who were not. These findings were supported by a second meta-analysis conducted the same year, which found that abstinence increased by 63% with the use of SMS-based interventions [15].

Our research group has previously investigated the use of an SMS-based intervention (NEXit) for smoking cessation among university students in Sweden [16-18]. The intervention was evaluated using a two-arm, parallel-group randomized controlled trial including 1590 participants between the ages of 21 and 30 years. With respect to 8-week prolonged abstinence, a statistically significant difference was found between the intervention group (25.9%) and control group (14.6%). Differences in the 4-week point prevalence between the groups were also statistically significant (20.6% versus 14.2%). The intervention has now been adapted to a younger age group and is currently in trial among high-school students in Sweden [19].

There is, however, no research in Sweden or elsewhere on the use of SMS-based interventions for smoking cessation prior to surgery. Given the success of the approach in other contexts and the importance of smoking cessation prior to surgery, it is valuable to determine if such an approach could work in this context.

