### Statistical Analysis

#### Methods

All analyses will be performed under the intention-to-treat principle, where all randomized individuals will be included. Missing outcome data will initially be handled using complete-case analysis, which assumes that data are missing at random. If data are systematically missing, it may be possible that early responders differ from late responders, and in extension, that late responders are more similar to nonresponders. We will therefore explore the plausibility of the missing-at-random assumption by regressing the primary outcomes on the number of follow-up attempts needed before a response was recorded. To further explore the missing-at-random assumption, attrition will be investigated among study groups by comparing baseline characteristics between those who did and those who did not respond at follow-up. A sensitivity analysis that includes imputed values for missing outcome data (using multiple imputation by chained equations) will also be performed. Data will be graphically examined for outliers or data input errors, and sensitivity analyses will be performed while excluding any erroneous data points.

#### Hypothesis 1

Primary outcome measures and 7-day point prevalence of smoking abstinence will be analyzed using logistic regression. Negative binomial regression will be used to analyze the number of quit attempts, other smoking cessation services used, and cigarettes smoked weekly. Both unadjusted and adjusted models (primary) will be investigated. The following baseline characteristics will be adjusted for all models: gender, age, years of smoking, mean number of cigarettes smoked weekly, use of snuff, Fagerströms Nicotine Dependence Scale [40], importance, and self-efficacy.

Effect-modification analyses will be performed for the two primary outcomes. The following potential effect modifiers measured at baseline will be explored: gender, age, years of smoking, mean number of cigarettes smoked weekly, use of snuff, Fagerström Nicotine Dependence Scale, importance, and self-efficacy. Each effect-modification analysis will be performed by comparing adjusted logistic regression models excluding and including the interaction parameter using the likelihood ratio test.

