### Power Calculation

A previous study that explored the effect of an SMS-based smoking-cessation intervention for Swedish university students found that 25.9% in the intervention group had not smoked more than 5 cigarettes in the past 8 weeks compared to 14.6% in the control group [16]. This is comparable to a Cohen *d* value of 0.3, which can be interpreted as a small-to-medium effect. In general, this is in line with what we should expect from brief digital lifestyle interventions. In order to identify a statistically significant difference between the two groups, under the expected Cohen *d* value of 0.3, we will need to recruit 192 patients per group (at 0.8 power and .05 significance level). Assuming a 10% loss to follow-up, the final sample size required is 434 patients.

With 20 surgical departments recruiting participants over 12 months, we would require each department to recruit an average of 1.8 participants each month. If necessary, the recruitment period of 30 months will require 0.7 recruited participants on an average per month per department. We believe that this is feasible, given the commitment from the departments.

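### As written, weekly cigarettes are compared between arms only among people still smoking, a post-randomisation group, which conflicts with the statement that all analyses include everyone randomised

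*Protocol article*

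**What the plan says.** Under Measures, the protocol article lists among the secondary outcomes the "number of cigarettes smoked weekly (if still smoking". The phrase still smoking is not defined. The primary outcomes are abstinence measures: "Primary outcome measures: Prolonged abstinence and point prevalence of smoking abstinence".

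Under Statistical Analysis, Hypothesis 1, the model is given: "Negative binomial regression will be used to analyze the number of quit attempts, other smoking cessation services used, and cigarettes smoked weekly". This sentence does not repeat the restriction to smokers. Unadjusted and adjusted models are both planned, with the adjusted one primary. The covariates are "gender, age, years of smoking, mean number of cigarettes smoked weekly, use of snuff, Fagerströms Nicotine Dependence Scale [40], importance, and self-efficacy". The paragraph before Hypothesis 2 applies two-sided tests at .05 to all models.

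The opening of the Statistical Analysis section states: "All analyses will be performed under the intention-to-treat principle, where all randomized individuals will be included". The article gives no value for participants who have stopped smoking and no two-part model. The Discussion calls analyses of secondary outcomes preliminary and exploratory, because the trial was powered for the two primary outcomes.

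**The concern.** Whether a participant still smokes at follow-up is decided after randomisation, and the intervention aims to change it. If it works, it removes more people from the smokers-only comparison in its own arm. If those extra quitters were lighter smokers, the smokers left behind are heavier on average. The comparison then leans against the intervention even when no continuing smoker has changed consumption, and it can hide a modest real reduction. A larger trial would not remove this bias.

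The two passages also cannot both hold. An outcome that exists only for smokers cannot be analysed in all randomised individuals. The choice affects the planned multiple imputation too: if quitters' values are coded as missing, the imputation could assign cigarettes to people who have stopped.

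**Working it through.** The protocol states no figure for this outcome, so there is none to reproduce. Inputs from the protocol are:
- 192 per group and prolonged abstinence of 25.9% versus 14.6% (Power Calculation)
- 4-week point prevalence in the earlier student trial of 20.6% versus 14.2% (Previous Research and Findings)

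The consumption distribution and its link with quitting are assumptions, because the protocol gives neither.

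**1. Who is left.** Number still smoking = 192 × (1 − abstinence rate).
- Prolonged abstinence: 192 × 0.741 = 142 versus 192 × 0.854 = 164.
- 4-week rates: 192 × 0.794 = 152 versus 192 × 0.858 = 165.

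**2. How the two ratios are linked.** With quitters at 0, the ratio over everyone = [(1 − p_I)/(1 − p_C)] × smokers-only ratio. The first factor is 0.741/0.854 = 0.868 at the planning rates and 0.794/0.858 = 0.925 at the 4-week rates.

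**3. Hand example (assumed).** Half the patients smoke 35 a week and half 105. Control quitting is unrelated to consumption. The intervention's extra quitters are all light smokers, and continuing smokers do not change.
- Planning rates: 37.2% of light and 14.6% of heavy smokers quit on intervention (average 25.9%). The smokers-only mean is (0.314 × 35 + 0.427 × 105)/0.741 = 75.3, against 70.0 in control, a ratio of 1.08. Over everyone: 55.8/59.8 = 0.93.
- 4-week rates: 27.0% and 14.2% quit (average 20.6%). The smokers-only mean is (0.365 × 35 + 0.429 × 105)/0.794 = 72.8, against 70.0, a ratio of 1.04. Over everyone: 57.8/60.1 = 0.96.

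**4. Large simulations at the planning rates, no effect on continuing smokers, quitting driven only by baseline consumption (mean 70 a week).**
- Log-normal consumption (SD of log 0.6), lighter smokers quitting more: the unadjusted smokers-only ratio runs from 1.034 to 1.103, and the ratio over everyone from 0.897 to 0.957. If quitting is unrelated to consumption, they are 1.00 and 0.868.
- Gamma consumption: unadjusted 1.03 to 1.10. Adjusting for log baseline consumption gives 1.00. Entering baseline untransformed leaves 1.01 to 1.04.
- A further gamma set gave ratios over everyone of 0.894 to 0.939.

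**5. The same with an unmeasured determinant added** (log-scale SD 0.5 measured, 0.4 unmeasured; both affect consumption and quitting). The model is negative binomial, and the adjusted version includes the measured part. Slopes are log-odds of quitting per log-unit of consumption.

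| Slope, control / intervention | True ratio in continuing smokers | Smokers only, unadjusted | Smokers only, adjusted | Everyone, quitters at 0 |
|---|---|---|---|---|
| 0 / 0 | 1.00 | 0.999 | 1.000 | 0.864 |
| −1 / −1 | 1.00 | 1.043 | 1.017 | 0.905 |
| −0.5 / −1.5 | 1.00 | 1.088 | 1.041 | 0.943 |
| −1 / −2 | 1.00 | 1.087 | 1.041 | 0.945 |
| −1 / −1 | 0.95 | 0.994 | 0.967 | 0.861 |
| −0.5 / −1.5 | 0.95 | 1.040 | 0.988 | 0.898 |
| −1 / −2 | 0.95 | 1.036 | 0.989 | 0.900 |

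A separate run with an unmeasured determinant gave adjusted ratios of about 1.04 to 1.06.

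**6. Against sampling noise.** With an assumed coefficient of variation of 0.9, the standard error of the unadjusted log ratio is √(0.81/142 + 0.81/164) = 0.10. A 4% bias is 0.039 on the log scale, and a 6% bias is 0.058.

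**The case against.** The strongest reply is that the planned primary model already adjusts for baseline cigarettes, nicotine dependence, importance and self-efficacy. This stands in large part. Where quitting depends only on baseline consumption, adjustment on a suitable scale removes the bias. A remainder of about 2% to 6% needs an unmeasured determinant, which is plausible but not documented. That remainder is also smaller than the likely standard error.

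Second, the words about still smoking sit in the list of measures and may only describe a questionnaire skip, while the analysis sentence carries no restriction. Zero for quitters may therefore have been intended; the questionnaires are in an appendix that is not shown. This makes the conflict one to be reconciled. It does not make the restriction harmless if it is applied as written.

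Third, the protocol labels secondary outcomes exploratory. True, but the label rests on power and does not tell the reader that this comparison is not a randomised one.

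A reader might infer more: that the trial will show a false increase in smoking, or that the group is defined exactly by a primary outcome. The documents support neither. The direction depends on who quits, and the ratio is 1.00 if quitting is unrelated to consumption. Still smoking is undefined, and prolonged abstinence tolerates up to 5 cigarettes in 8 weeks, so the smokers need not be exactly those who fail a primary outcome.

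**Conclusion.** The point holds for one secondary outcome. As written, it conditions on a post-randomisation state that the intervention targets, and it conflicts with the stated analysis population. If lighter smokers quit more readily and continuing smokers do not change, the smokers-only ratio is biased upwards to about 1.03–1.10 unadjusted. In the primary adjusted model it is about 1.00–1.04, or about 1.02–1.06 with unmeasured determinants. The ratio over everyone, with quitters at 0, is about 0.89–0.96. These simulated sizes rest on assumed consumption and on the prolonged-abstinence planning rates. The gap in the 4-week rates is smaller (6.4 rather than 11.3 points), and so is the bias in the hand example (1.04 rather than 1.08). The abstinence analyses, including both primary outcomes, are not restricted to smokers and are unaffected.

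**What to change.** Reconcile Measures with Statistical Analysis. Define weekly cigarettes for all participants, with abstainers at 0, and say which answer establishes abstinence for this purpose. Base inference on the overall mean ratio, from a negative binomial model with robust standard errors or as the marginal mean of a hurdle model. The hurdle model's positive part should not carry the inference, because it conditions on smoking in the same way. Show continuing-smoker figures descriptively only.

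One detail needs care. Under Follow-Up, phone calls collect the primary outcomes only. A quitter reached by phone would have a known 0, while a smoker reached by phone would have no count, so quitters would be selectively included. Either apply the zero rule to questionnaire respondents only, or impute counts for smokers reached by phone.

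The cost is wording, plus imputation if that route is chosen; no added patients or visits are needed. The downsides are small: the distribution has more zeros, and the overall ratio mixes quitting with reduction, so it should be read beside the abstinence results.

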### Statistical Analysis

#### Methods

All analyses will be performed under the intention-to-treat principle, where all randomized individuals will be included. Missing outcome data will initially be handled using complete-case analysis, which assumes that data are missing at random. If data are systematically missing, it may be possible that early responders differ from late responders, and in extension, that late responders are more similar to nonresponders. We will therefore explore the plausibility of the missing-at-random assumption by regressing the primary outcomes on the number of follow-up attempts needed before a response was recorded. To further explore the missing-at-random assumption, attrition will be investigated among study groups by comparing baseline characteristics between those who did and those who did not respond at follow-up. A sensitivity analysis that includes imputed values for missing outcome data (using multiple imputation by chained equations) will also be performed. Data will be graphically examined for outliers or data input errors, and sensitivity analyses will be performed while excluding any erroneous data points.

#### Hypothesis 1

Primary outcome measures and 7-day point prevalence of smoking abstinence will be analyzed using logistic regression. Negative binomial regression will be used to analyze the number of quit attempts, other smoking cessation services used, and cigarettes smoked weekly. Both unadjusted and adjusted models (primary) will be investigated. The following baseline characteristics will be adjusted for all models: gender, age, years of smoking, mean number of cigarettes smoked weekly, use of snuff, Fagerströms Nicotine Dependence Scale [40], importance, and self-efficacy.

Effect-modification analyses will be performed for the two primary outcomes. The following potential effect modifiers measured at baseline will be explored: gender, age, years of smoking, mean number of cigarettes smoked weekly, use of snuff, Fagerström Nicotine Dependence Scale, importance, and self-efficacy. Each effect-modification analysis will be performed by comparing adjusted logistic regression models excluding and including the interaction parameter using the likelihood ratio test.

For all models, coefficients of interest will be assessed for statistical significance using a null hypothesis testing approach, where tests will be two-tailed at the .05 significance level with 95% CIs. Alongside the null hypothesis tests, posterior distributions using a Bayesian approach will be calculated for each coefficient [41]. Both significance tests and posterior distributions will create a basis for scientific inference.

#### Hypothesis 2

Mediators will be explored using a causal inference framework [42], where Monte Carlo methods are relied upon for inference. This allows for any type of model (linear and nonlinear) to be used to represent the relationships between the group allocation, mediating variable, and the outcome. Three models will be created for each outcome measure, two of which investigate the mediating factors on their own and a third that incorporates both mediators at once. If any baseline characteristics are found to moderate the effect in the primary analysis, additional mediator models will be created to include these characteristics as moderators.

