### Aims and Hypotheses

There is strong evidence that short-term smoking cessation before surgery can reduce postoperative complications and morbidity. There are, however, several structural problems in the Swedish health care system concerning the organization of smoking cessation for patients waiting for surgery. The overall aim of this project is to fill the knowledge gap on whether an SMS-based smoking-cessation intervention can be effective in helping patients stop smoking preoperatively. This trial protocol includes a two-arm parallel-group randomized controlled trial that aims to evaluate the effectiveness of the SMS-based intervention on smoking behavior as a tool in addition to the current routine treatment and to measure potential mediators of the intervention on smoking cessation.

There are two hypotheses in this study: (1) Smoking outcome measures will differ between the two groups at 3, 6, and 12 months after randomization. The 3-month period will be the primary time point. (2) Importance of smoking cessation and self-efficacy will mediate the effects of the intervention on smoking outcomes at 3 months. The same measures at 3 months will mediate the effect of the intervention at 6 months (and 6 months on 12 months).

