A limitation of this study is that is that it does not include cessation of smoke-free tobacco (such as snuff). To our knowledge, no studies have thus far identified an association between smoke-free tobacco and postoperative complications. Thus, the benefits of an intervention targeting smoke-free tobacco will have to be evaluated in a separate trial. Another limitation is the use of nonbiochemical verification at follow-up. However, the Society for Research on Nicotine and Tobacco recommends that in population-based studies with limited face-to-face contact, it is neither required nor desirable to use biochemical verification [39]. Finally, this trial has been designed to power the statistical analyses of two primary outcome measures; thus, analyses of secondary outcome measures and mediation measures should be regarded as preliminary and exploratory work.

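### Two unranked primary outcomes are each tested at two-sided .05 with no rule for what counts as success, so the plan cannot hold both its stated alpha and its stated power

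*Protocol article*

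**What the plan says.** All references are to the protocol article.

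- **Outcomes.** Under Measures: "Primary outcome measures: Prolonged abstinence and point prevalence of smoking abstinence". The two are not ranked. The limitations in the Discussion repeat that "this trial has been designed to power the statistical analyses of two primary outcome measures".
- **Testing rule.** The close of Statistical Analysis, Hypothesis 1, states: "For all models, coefficients of interest will be assessed for statistical significance using a null hypothesis testing approach", and adds that "tests will be two-tailed at the .05 significance level with 95% CIs".
- **Second basis.** The same paragraph has a posterior calculated for each coefficient and concludes: "Both significance tests and posterior distributions will create a basis for scientific inference". It gives no posterior threshold and no rule for disagreement.
- **Priorities that are set.** Aims and Hypotheses: "The 3-month period will be the primary time point". Statistical Analysis, Hypothesis 1: "Both unadjusted and adjusted models (primary) will be investigated". These rank time points and models. Neither ranks the two outcomes.
- **Sample size.** Power Calculation uses one outcome only, prolonged abstinence, from an earlier trial in students: "25.9% in the intervention group had not smoked more than 5 cigarettes in the past 8 weeks compared to 14.6% in the control group". It arrives at 192 per group at power 0.8 and significance level .05, and at 434 after 10% loss.

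**The concern.** The two tests do not serve two separate questions. Aims and Hypotheses puts both outcomes under one hypothesis, and the Discussion ties the trial to one decision, whether to offer the intervention to all surgical departments in Sweden. A significant result on either outcome could be used to support that decision.

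The plan does not say what the trial concludes if one primary outcome is significant and the other is not. Without a rule, the choice falls to people who have seen the data, and the stated .05 no longer describes the error behind the conclusion. The gap cannot be filled harmlessly later, because the two obvious rules have different costs: either-suffices raises the error, and both-must-succeed lowers the power. The paired use of tests and posteriors leaves a second open choice of the same kind.

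**Working it through.** **Inputs**

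- Prolonged abstinence 25.9% v 14.6%; 192 per group; power 0.8; .05; 10% loss; N = 434 (Power Calculation).
- Point prevalence 20.6% v 14.2% in the same earlier trial (Previous Research and Findings; not used in Power Calculation).
- Correlation r between the two test statistics: not given, so an assumption. At 3 months the 4-week window lies inside the 8-week window, so the outcomes overlap strongly. They are not identical, since one allows up to 5 cigarettes and the other none. I take 0.5 to 0.9 as plausible and also show 0.

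**1. The plan's own sample size**

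Arcsine effect size: h = 2(asin√0.259 − asin√0.146) = 0.284.

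n per group = 2[(1.960 + 0.842)/h]² = 195, within 3% of the stated 192.

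Allowing for loss: 195/0.9 = 216.7, so 217 per group and 434 in total, as stated. The figure is therefore reproduced with an unsplit .05 on prolonged abstinence alone.

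**2. If either outcome suffices**

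With both nulls true:

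- any false-positive primary result = 1 − P(|Z₁| < 1.96 and |Z₂| < 1.96)
- a false claim of benefit = 1 − P(Z₁ < 1.96 and Z₂ < 1.96)

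At r = 0 these are 1 − 0.95² = 9.75% and 1 − 0.975² = 4.94%. Other values come from the bivariate normal distribution.

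| r (assumed) | Either direction | False benefit |
|---|---|---|
| 0 | 9.75% | 4.9% |
| 0.5 | 9.1% | 4.5% |
| 0.7 | 8.3% | 4.2% |
| 0.8 | 7.8% | 3.9% |
| 0.9 | 7.0% | 3.5% |
| One test alone | 5% | 2.5% |

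**3. If both must succeed**

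Error is at most 5%. Joint power cannot exceed the lower of the two single powers. With n = 192 and pooled variance under the null, power = Φ[(|p₁ − p₂|√n − 1.96√(2p̄q̄)) / √(p₁q₁ + p₂q₂)].

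- Prolonged abstinence: (0.113 × 13.856 − 1.96 × 0.5683)/0.5627 = 0.80, power 79%.
- Point prevalence: (0.064 × 13.856 − 1.96 × 0.5361)/0.5342 = −0.31, power 38%.

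Joint power is therefore at most about 38%. By the same method, 80% power for point prevalence would need 550 per group.

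**4. How often the outcomes would disagree**

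At those rates, the chance that prolonged abstinence is significant and point prevalence is not is at least 79 − 38 = 41 percentage points, whatever the correlation.

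**5. Remedies compared**

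- Bonferroni (.025 each): familywise error 4.65% at r = 0.5 and 3.62% at r = 0.9. Power for prolonged abstinence falls from about 79-80% to about 70-71%. Keeping 80% needs about 237 to 240 per group, which is 264 to 267 after 10% loss, or 528 to 534 in total.
- Fixed sequence: error at most 5%, with N = 434 and the power of the first outcome unchanged.

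**The case against.** **The excess error is conditional.** The article never says that one significant outcome is enough. A reader might infer that the trial's false-positive rate simply exceeds 5%; the text supports this only under the either-suffices reading. That objection stands, and it is why both readings are worked out above. It does not remove the problem, because the other reading gives up the stated power.

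**The familywise figure counts harm as well as benefit.** This is right. A false claim of benefit on at least one outcome stays below 5%. It is still above the 2.5% that one two-sided .05 test allows in that direction.

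**The independence figure is unrealistic.** Also right. With overlapping definitions, 9.75% is a ceiling only.

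**The posteriors.** A reader might infer that a posterior counts equally with the test, or that a favourable posterior can override a non-significant result. The article says neither; a joint reading of the two is at least as natural. Equating the posterior with a laxer test would need a prior and a cut-off that the article does not give. With a flat prior and a 95% credible interval, the posterior would roughly reproduce the .05 test. What remains is that no rule says which one decides.

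**The 38% rests on rates from university students** that Power Calculation does not use for this outcome. This is fair, and the figure is conditional on those rates. However, they come from the same trial that supplied the planning rates for prolonged abstinence, and the Discussion says that both outcomes are powered.

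**A separate analysis plan may hold the rule.** It may. But the article does not merely stay silent: it fixes .05 for all models, names two primaries and spends the whole .05 on one of them. An unseen plan does not reconcile those statements.

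**Conclusion.** The point holds in conditional form: the success rule across the two primary outcomes is unstated, and neither natural rule preserves what the article promises.

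- **Either suffices:** familywise two-sided error about 7-9% and false benefit about 3.5-4.5%, assuming a correlation of 0.5 to 0.9.
- **Both required:** error controlled, but power at most about 38%, assuming the earlier trial's point-prevalence rates.

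The contribution of the posteriors to error cannot be quantified, and no figure is attached to it. The 38% bears on disagreement between the two outcomes; it says nothing about a test and a posterior disagreeing on the same coefficient. A reader might also want to add the 6- and 12-month tests to the error count; that is not supported, because 3 months is named as the primary time point. Since this governs the trial's main conclusion, it should be settled before outcome data are seen.

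**What to change.** State the following in the protocol or analysis plan:

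1. At 3 months, in the adjusted logistic model, test prolonged abstinence at two-sided .05.
2. Test 4-week point prevalence at two-sided .05 only if the first test is significant.
3. The significance test decides; the posterior distributions are supportive description.

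Putting prolonged abstinence first follows the protocol's own choice of that outcome for the sample size. A both-must-succeed rule would also control error, at the power shown above.

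The cost is a few lines of text and the loss of a stand-alone claim on point prevalence, which has little power at the earlier trial's rates. The Discussion sentence on powering two primary outcomes should be brought into line with Power Calculation, which covers one.
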